**Methods:**

This study involves a community-based cluster randomised trial conducted at Primary Healthcare Centres in the Community of Madrid (Spain). The project aims to evaluate the effectiveness of an educational group intervention performed by primary healthcare professionals in increasing the proportion of mother-infant pairs using exclusive breastfeeding at six months compared to routine practice.

The number of patients required will be 432 (216 in each arm). All mother-infant pairs using exclusive breastfeeding that seek care or information at healthcare centres will be included, as long as the infant is not older than four weeks, and the mother has used exclusive breastfeeding in the last 24 h and who gives consent to participate.

The main response variable is mother-infant pairs using exclusive breast-feeding at six months.

Main effectiveness will be analysed by comparing the proportion of mother-infant pairs using exclusive breast-feeding at six months between the intervention group and the control group. All statistical tests will be performed with intention-to-treat. The estimation will be adjusted using an explanatory logistic regression model. A survival analysis will be used to compare the two groups using the log-rank test to assess the effect of the intervention on the duration of breastfeeding. The control of potential confounding variables will be performed through the construction of Cox regression models.

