### Prevalence of breast-feeding in developed countries: Associated factors

In spite of the broad dissemination of recommendations to promote EBF and its benefits, only 35% of newborns around the world receive EBF after the first three or four months of life [15]. The rates are much lower than those set out by the WHO in European countries, and specifically, in Spain the rates are similar to the rest of the developed countries, with 24.72% EBF at six months, and slightly lower in the Region of Madrid (23.54%) [16].

In Spain the average length of breastfeeding is around 3–5 months. The greater number of abandonments of EBF takes place during the first 4 weeks, (sometimes up to one third of cases) and between the 3rd and 4th months of life, which coincides with the imminent return of the mother to work [17–20].

According to the results of an observational study in Spain the factors that influence the continuity of EBF up to six months are diverse: lack of confidence to breast-feed, pain, suction problems, cracks, infections, ingurgitation, mastitis, baby crying, type of birth, execution of early skin to skin contact, bad experience with prior breast-feeding, comments by family members and/or friends, aspects related with going back to work, and the socio-economic and education level of the mother [21, 22]. Other authors point out the possible effect that the model of the breast-feeding mothers’ mothers, women that lived during periods of setbacks regarding the prevalence of breast-feeding, many of whom most likely did not breast-feed, could have on the breast-feeding mother’s [14].

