#### Inclusion criteria

Professionals of the randomization unit (CS):
Minimum of 2 years working as a professional in PHC.Have no intention of transferring during the study period.Provide healthcare to the infant population within their daily healthcare workload.Sign the researcher agreement.

Mother-infant dyad:
Mothers of full-term newborns and that use EBF ≥ 18 years of age at the selection visitFull-term newborns (≥ 37 weeks of gestation), with a birth weight > 2.5 kg and with the newborn’s age ≤ 4 weeks.

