#### Exclusion criteria

Professionals of the randomization unit (CS):
Those that reject participation in the study.

Mother-child pairs:
Clinical conditions of the mother that contraindicate breast-feeding: active tuberculosis, active chicken pox, active Herpes lesions on breasts, Chagas disease; human immunodeficiency virus (HIV); human T-lymphotropic virus (HTLV) I and II; substance abuse; mother in treatment with radioactive isotopes or chemotherapy or antimetabolite drugs.Clinical conditions of the child that complicate or impede breast-feeding, orofacial malformations.Clinical conditions of the child that contraindicate breast-feeding: classic galactosemia (galactose-1-phosphate uridyltransferase deficiency) in newborns.Infants that have been initiated on complementary feeding.Women that do not consent to participating in the study.Impossibility of the mother to come to the visits proposed for the conduction of the study.Difficulties with the language that impede or complicate communication between the mother and the healthcare professionals.Women that are participating in another research study during the study period.

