### Variables

#### Outcome variables

The main outcome variable is the percentage of infants who continue exclusively breastfed at six months.

The secondary outcome variables will be:Type of feeding at six months (categorical: EBF, PBF, CF).Duration of EBF (days) = (Date of abandonment EBF – Date of birth of infant).Reasons for abandonment of BF (semi-structured questionnaire created for the study).Number of group education sessions to which the dyad attends. Adequate adherence is considered as attendance to at least 85% of the planned sessions.Degree of satisfaction with the educational group intervention (measurement instrument: SERVQUAL).

The prognostic variables will be:For the professional: age (years), sex, breastfeeding training received.For the mother: age (years); education level (low – primary studies only; medium - high school completed, technical training or other non-university studies completed; high - university level education completed); income level; nationality; working situation of the mother (if she works outside the home and the number of hours per working day/ days per week); living situation with partner; obstetric history (pregnancies/abortions/live births); type of birth (vaginal/caesarean; single/multiple); Previous breastfeeding experience; peso(kg); size(cm); smoker (yes/no).For the newborn: single foetus (YES/NO); sex; birth-weight (grams); discharged from hospital with mother (YES/NO); APGAR test, separation from the mother during hospital stay (YES/NO); breast-fed during first hours after birth (YES/NO).Regarding breast-feeding: intention to breast-feed (only mother’s milk/only formula/both/I don’t know); received support for breast-feeding during pregnancy (YES/NO); received support for breast-feeding in the hospital (assessment of the attention received in the hospital regarding breast-feeding using the BFHI test); family support measured using the Apgar family test [34]; if breast-feeding took place in the first 30 min.; self-efficacy in breast-feeding measured using the Breastfeeding Self-Efficacy Scale-Short Form (BSES-SF) (test validated in Spain with a global score of 0 to 100); cracks or mastitis in the first 8 days; schedule limitation of feedings.

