4. Analysis of secondary effectiveness. To evaluate the effect of the educational group intervention on the duration of the different types of breast-feeding, an analysis of survival will be done, making the comparison between the two groups using the log-rank test. The control of the possible confounding variable will be done with the construction of different Cox regression models. The proportion of women that attend at least 85% of the planned sessions will be calculated to study the degree of adherence. The women’s satisfaction with the educational group intervention will be measured with a Likert-type scale.

All *p*-values below 0.05 will be considered as statistically significant for all cases.

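### Duration of exclusive breastfeeding is counted from birth, but pairs come under observation only at enrolment and only if still exclusively breastfeeding, so the survival analysis needs delayed entry

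*Protocol article*

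**What the plan says.** Four parts of the Protocol article bear on this.

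- **Time origin.** Outcome variables, secondary list: "Duration of EBF (days) = (Date of abandonment EBF – Date of birth of infant".
- **Entry rule.** The abstract admits pairs "as long as the infant is not older than four weeks, and the mother has used exclusive breastfeeding in the last 24 h". The inclusion criteria repeat the age limit ("with the newborn’s age ≤ 4 weeks"), and the exclusion criteria remove "Infants that have been initiated on complementary feeding". A pair that stopped EBF before it would have been approached is therefore never in the data.
- **Analysis.** Statistical analysis, item 4: "an analysis of survival will be done, making the comparison between the two groups using the log-rank test", followed by "The control of the possible confounding variable will be done with the construction of different Cox regression models". Neither delayed entry nor a landmark is mentioned, and the infant's age at enrolment is not among the listed prognostic variables.
- **When events occur.** The background on prevalence says: "The greater number of abandonments of EBF takes place during the first 4 weeks, (sometimes up to one third of cases".

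On recruitment, Table 1 places randomisation of centres two months before visit 1. The Intervention section has the professionals who deliver the assigned arm also recruit, and the Masking section says the intervention cannot be masked.

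**The concern.** This is left truncation. With birth as time zero and no entry time, every pair sits in the risk set from day 0, although it was guaranteed event-free until its enrolment day. The uncounted events fall in the window where the article itself places the peak of abandonment.

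Two consequences need to be kept apart. The first is descriptive: survival curves and medians from birth are too long in both arms, even with perfect balance. It matters if they are set beside population figures such as the 3–5 month average duration in the background section. The second is comparative and conditional: if one arm enrols later, it is credited with more guaranteed event-free time and looks better with no intervention effect. The bias reverses if that arm enrols earlier.

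**Working it through.** **The plan's own figures.** None is given for duration. The sample size reproduces: 24% against 39%, two-sided 5%, 80% power, no continuity correction, gives 150 per group; 150 × 1.29 = 193.5, rounded up to 194; 194/0.90 = 215.6, rounded up to 216. The simulations below use 194 pairs per arm.

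**Inputs.** 24% on EBF at six months (Sample size), applied here to all mothers who start EBF and placed at day 182 (assumptions). Proportion *e* stopping by day 28: 1/3 is the background section's upper figure; 20% is an assumed milder case. If one third of cases means one third of abandonments, then *e* = (1 − 0.24)/3 = 25%, between the two. The hazard is taken as constant within days 0–28 and within days 28–182.

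**True median among all starters.** With h₂ = ln[(1 − e)/0.24]/154, the median is 28 + ln[(1 − e)/0.5]/h₂.

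- e = 1/3: h₂ = 1.0217/154 = 0.00663; 28 + 0.2877/0.00663 = 71 days.
- e = 20%: h₂ = 1.2040/154 = 0.00782; 28 + 0.4700/0.00782 = 88 days.

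**Apparent median, everyone at risk from day 0.** If entry age is uniform over days 0–28 among enrolled pairs, apparent EBF at day 28 is the average of S(28)/S(a), which equals e/[−ln(1 − e)].

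- e = 1/3: 0.333/0.4055 = 82%, against a true 67%. Median 28 + ln(0.822/0.5)/0.00663 = 103 days.
- e = 20%: 0.20/0.2231 = 90%, against a true 80%. Median 28 + ln(0.896/0.5)/0.00782 = 103 days.

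If entry is uniform among all starters instead, the medians are 101 and 102 days. Simulation gave 101–104 and 102. With delayed entry it returned 71–72 and 88.

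**Arm comparison under no true effect.** Independent pairs, 2,000 runs per scenario, log-rank at nominal 5%. The hazard ratio (HR) is for stopping EBF in the later-enrolling arm.

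| Gap in mean entry age | Ordinary, e = 1/3 | Ordinary, e = 20% | Delayed entry |
|---|---|---|---|
| 0 days | 5%, HR 1.00 | 6%, HR 1.00 | 5–6% |
| 7 days (days 7–28 v 0–21) | 21%, HR 0.88 | 9%, HR 0.93 | 5% |
| 14 days (days 14–28 v 0–14) | 62%, HR 0.76 | 25%, HR 0.86 | 5–6% |

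Repeat simulations agreed within about two percentage points (19–21% and 60–62% for e = 1/3; about 24% for the 14-day gap at e = 20%).

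**Clustering.** Dividing the test statistic by √1.29 = 1.136, from the plan's own design effect, turns 21% into about 17%, 60% into about 50%, and 9% into about 8%.

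**Alternatives.** Restarting the clock at enrolment is not a full cure: with e = 1/3 and a 14-day gap it still rejects in 20% of runs (HR 0.87). A day-28 landmark does work (4–6%, HR 1.00).

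**Power.** With equal entry ages and a hazard ratio of 0.7 after day 28, ordinary and delayed-entry log-rank both reject in 54% of runs, so delayed entry loses nothing there.

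**The case against.** The strongest reply is that no quoted sentence is wrong in itself. Days since birth are correct for each enrolled pair, birth is a sensible origin, and log-rank and Cox remain log-rank and Cox when run with delayed entry. An analysis plan that is not shown could specify it. That has weight. But the article does fix the origin, the entry rule and the tests, and the default form of those tests on that duration is the faulty one.

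Other parts of the reply stand and limit the point.

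- A reader might infer that the arm comparison is biased. The documents do not support this: they give no enrolment ages, and consecutive sampling and the same visit 1 window apply to both arms. Unmasked recruitment after allocation makes a gap possible; it does not show one.
- A reader might take the figure of about 60% as the expected size. It needs the upper early-loss figure, entry windows that do not overlap, and no allowance for clustering.
- The medians are too long relative to all mothers who start EBF. The trial's subjects are pairs already on EBF at contact, and it states no aim of estimating population duration.
- Duration is a secondary outcome, absent from the listed objectives. The primary comparison is a proportion at six months and does not use this time scale.

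**Conclusion.** The point holds for the secondary analysis of EBF duration. Followed in its ordinary form, that analysis counts pairs as at risk on days when they could not have had an event.

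The overstatement of the median needs no imbalance between arms. It is roughly 30 days if one third stop by day 28 and roughly 14 days if 20% do, assuming entry spread over the four weeks and piecewise constant hazards.

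Bias between arms is conditional on different enrolment ages. False positives would be about 9–21% for a 7-day gap and about 24–61% for an extreme 14-day gap, somewhat lower with clustering. At equal entry ages the test keeps its level. The gaps and the 20% case are assumptions, not figures from the article.

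This does not show that the trial's duration result will be wrong, nor that the origin should be moved from birth.

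**What to change.** Add a sentence to item 4 of the Statistical analysis: time is age since birth, and each pair enters the risk set at its age on the visit 1 (consent) date, for Kaplan-Meier, log-rank and Cox alike, alongside the allowance for clustering already promised. Confirm that the electronic case report form captures that date; Table 1 places consent and recruitment at visit 1, but neither the date nor the infant's age at enrolment is in the variable list. Report enrolment age by arm. A day-28 landmark is a reasonable sensitivity analysis.

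The cost is one more variable in the survival command, somewhat fewer pairs at risk in the first four weeks, and a less favourable median in both arms.

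Two limits should be stated with it. Delayed entry removes the guaranteed event-free time, but not bias from staff recruiting pairs according to prognosis. It also recovers the median from birth only if some pairs enrol soon after birth: with entry confined to days 14–28 and one third early loss, the delayed-entry median was about 102 days, because the curve then describes only pairs still on EBF at about day 14. If early enrolment is sparse, the curve should be labelled as conditional on reaching the earliest entry age.

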### Data collection method

The information will be incorporated into an electronic case report form (eCRF), ensuring confidentiality and anonymity, and guaranteeing compliance with current regulations. The age of the mothers that reject participation in the study will be recorded.

Likewise, the losses and abandonments during the study and their causes will be recorded. The mothers will be called by telephone to invite them to attend the education group sessions and to the monitoring of the control group.

Through the combination of our web-based, instantaneous electronic validation, the main researcher daily visual cross-validation of the data for complex errors, and regular on-site monitoring, the quality and completeness of the data will be reflective of the state of the art in clinical trials.

All Principal Investigators will be given access to the cleaned data sets. Project data sets will be housed on the Project Accept Web site created for the study, and all data sets will be password protected. Project Principal Investigators will have direct access to their own site’s data sets, and will have access to other sites data by request. To ensure confidentiality, data dispersed to project team members will be blinded of any identifying participant information.

### Statistical analysis

The database will be filtered before the statistical analysis is performed to improve the quality of the data collected. The use of the design by conglomerates will be taken into account in all phases of the analysis, especially when calculating the confidence intervals of the estimations and in the hypothesis tests. The following will be carried out:

1. Descriptive analysis of the demographic and baseline characteristics of the subjects of both groups. The quantitative variables will be described by their measurements of central, mean or median tendencies, in the case of asymmetrical distributions, and their measurements of dispersion, typical deviation or interquartile amplitude, respectively. The qualitative variables will be described by their proportion and confidence interval.

2. Initial comparability study of the two groups regarding their baseline characteristics, response variables and prognostic factors. The Student t test or the Mann-Whitney test will be used if the normality hypothesis is rejected for the data. If the study variables are qualitative, the Pearson’s Chi-squared test or Fisher’s exact test will be used, when applicable. In the case of inequality, the possible confounding factors will be defined by which the final analysis of the principal variable of effectiveness will be adjusted.

3. Principal analysis of effectiveness. The effect of the PROLACT intervention in the principal response variable: a comparison will be made of the proportion of mother/child pairs using EBF at six months in both groups, using Fisher’s exact test, while also estimating the confidence interval for the difference. If the confounding factors were distributed in an unequal manner in each group, a model will be constructed of explicative logistical regression where the dependent variable will be EBF at six months and the independent variable will be “treatment” group adjusted for the possible confounding factors. The analysis of effectiveness will be done by intention-to-treat.

4. Analysis of secondary effectiveness. To evaluate the effect of the educational group intervention on the duration of the different types of breast-feeding, an analysis of survival will be done, making the comparison between the two groups using the log-rank test. The control of the possible confounding variable will be done with the construction of different Cox regression models. The proportion of women that attend at least 85% of the planned sessions will be calculated to study the degree of adherence. The women’s satisfaction with the educational group intervention will be measured with a Likert-type scale.

All *p*-values below 0.05 will be considered as statistically significant for all cases.

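### Baseline comparisons between arms decide whether, and for what, the primary result is adjusted; the Abstract states adjustment without that condition

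*Protocol article*

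**What the plan says.** Three places in the protocol article bear on this.

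- **Statistical analysis, item 2.** The arms are compared on baseline characteristics and prognostic factors. For quantitative variables: "The Student t test or the Mann-Whitney test will be used if the normality hypothesis is rejected for the data". For the rest: "If the study variables are qualitative, the Pearson’s Chi-squared test or Fisher’s exact test will be used, when applicable". If the arms differ, "the possible confounding factors will be defined by which the final analysis of the principal variable of effectiveness will be adjusted".
- **Statistical analysis, item 3.** The primary outcome is first compared "using Fisher’s exact test, while also estimating the confidence interval for the difference". A second, conditional step follows: "If the confounding factors were distributed in an unequal manner in each group, a model will be constructed of explicative logistical regression", with treatment group as the explanatory variable and adjustment for the possible confounders.
- **Abstract, Methods.** The condition is absent: "The estimation will be adjusted using an explanatory logistic regression model".

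The section opens with a general statement: "The use of the design by conglomerates will be taken into account in all phases of the analysis, especially when calculating the confidence intervals", and it also names the hypothesis tests. The section closes by treating p-values below 0.05 as significant in all cases. The Variables section lists the prognostic variables but marks none as the adjustment set.

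**The concern.** This is a stated selection rule, not a detail left open. It picks covariates by whether the randomised arms happen to differ on them. What makes a covariate worth adjusting for is its relation to the outcome, and a baseline test carries no information on that. A strong predictor with a modest, non-significant imbalance is dropped, while a variable unrelated to breastfeeding enters if chance separates the arms.

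Three things are then unknown until the data are in: whether there is an adjusted estimate at all, which covariates it contains, and whether it or the unadjusted comparison carries the conclusion. Item 2 calls the adjusted analysis final, item 3 makes it conditional, and the Abstract treats it as given. If the two results fall on different sides of 0.05, the text does not settle which one counts.

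A further gap is that the tests named in items 2 and 3 are individual-level tests, and nothing shows how the opening promise on clustering is kept for them.

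**Working it through.** **The plan's own figures.** For 24% against 39%, two-sided 5% and 80% power:

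n = [1.96·√(2·0.315·0.685) + 0.842·√(0.24·0.76 + 0.39·0.61)]² / 0.15² = 149.4, so 150 per arm.

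Design effect 1 + 29 × 0.01 = 1.29; 150 × 1.29 = 193.5, so 194; 194/0.90 = 215.6, so 216 per arm and 432 in total. All stated figures reproduce.

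**Inputs**

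- Candidates: about 30, by count from the Variables section (3 for the professional, 12 for the mother, 7 for the newborn, 8 on breastfeeding).
- Cut-off for inequality: p<0.05. This is inferred from the general significance rule; item 2 gives none.
- Intra-class correlation: 0.01 (Sample size). The protocol gives it for the outcome; using it for baseline covariates is an assumption.
- Pairs per centre: 30 (Sample size), or 432/10 = 43.2 with the ten centres in Design of the study.

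**False-positive rate of one baseline test.** With design effect D = 1 + (m − 1) × ICC, an individual-level 5% test rejects with probability 2·[1 − Φ(1.96/√D)]. The expected number flagged is 30 times that and needs no independence. The chance of at least one does assume independence.

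| Setting | D | Rate per test | Expected of 30 | Chance of at least one |
|---|---|---|---|---|
| Tests respect clustering | 1 | 5.0% | 1.5 | 79% |
| Individual-level, 30 per centre | 1.29 | 8.4% | 2.5 | 93% |
| Individual-level, 43.2 per centre | 1.42 | 10.0% | 3.0 | 96% |

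Some listed variables nearly duplicate each other. With 20 distinct candidates the expected counts are 20 × 0.050 = 1.0, 20 × 0.084 = 1.7 and 20 × 0.100 = 2.0.

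**Check by simulation** (five centres of 43 per arm, ICC 0.01, no true difference): rejection was 9.6% for the t test, 10.2% for chi-squared and 8.3% for Fisher's test, against 4.2% for a t test on centre means.

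**Effect on the covariate set** (illustrative assumptions: 30 covariates with ICC 0.01, four of them prognostic at log odds ratio 0.4 per SD, 400 runs). The rule chose 3.1 covariates on average and picked each prognostic one only about 10% of the time. The treatment log odds ratio differed from that of the model with the four prognostic covariates by a median of 0.08 (90th percentile 0.19). Much of this is not error. The means were 0.65 and 0.72, and adjusting an odds ratio for strong predictors moves it away from the null even under perfect balance. The two analyses therefore estimate different quantities, which is one more reason to name the primary one. Mean divided by SD was 0.653/0.248 = 2.6 under the rule and 0.724/0.265 = 2.7 with the fixed set, so the gain in power in this example is modest.

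**The case against.** Four stronger readings are tempting, and the documents do not support them.

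- **That the tests ignore clustering.** The section says that the cluster design is respected in all phases and in the hypothesis tests. What stands is narrower: the tests named are individual-level and no cluster-aware version is given. Respecting clustering would still leave about 1.5 of 30 flagged.
- **That the whole primary result depends on chance.** The unadjusted comparison with its confidence interval is fixed and always done. Only the adjusted estimate, its content and the choice of final result depend on the data.
- **That the type I error of the treatment test is broken.** The rates above belong to baseline tests. The rule selects on imbalance, not on outcome. A simulation with no treatment effect (10 centres of 43, outcome clustered only through the covariates) gave treatment-test rejection of 5.0%, 4.8% and 4.8% after selection, at covariate ICC 0, 0.01 and 0.05. The fixed set gave 5.2%, 5.0% and 4.6%. Choosing between two available results is a separate risk, not quantified here.
- **That much higher flagging rates apply.** Rates near 27% per test need a covariate ICC of 0.05, which the protocol does not give.

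Two further objections have weight. Centres are randomised before pairs are recruited, and the recruiting professionals are not masked, so baseline differences may reflect real recruitment bias. Looking at balance is therefore useful. That argues for describing it and for a fixed prognostic set, not for letting a test choose the model. It is also fair that an article condenses, and that a covariate list often sits in an analysis plan that is not shown. But the article does not leave the matter open: it states a rule, which a later plan would have to replace. The Abstract's sentence may simply have lost its condition in shortening, but the two texts still differ.

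**Conclusion.** The point holds in this form. Covariates for the primary outcome are chosen by comparing randomised arms at baseline, and the adjusted model is conditional on the result. By chance alone about 1.5 of some 30 candidates would be flagged, or about 2.5 to 3 if the individual-level tests are applied as named. A true predictor is no more likely to be picked than an irrelevant variable. The consequences are an unpredictable covariate set, some lost precision, and no fixed answer to which result is primary, made worse by the difference between Abstract and item 3. An inflated error rate for the treatment test is not shown.

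The figures rest on the count of 30, the inferred cut-off of 0.05 and an ICC of 0.01 carried over from the outcome. The criticism of the rule itself needs none of them. The plan should be changed, but the trial does not fail on this point.

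**What to change.** - Remove baseline testing as the rule for choosing covariates. Keep the baseline comparison as description only.
- Name one primary analysis and the method by which it accounts for centre. With ten centres, candidates are a logistic model with a random centre effect and a small-sample correction, or a comparison of covariate-adjusted centre summaries.
- Adjust it for a short list fixed before data are seen, taken from listed variables measured before the intervention starts: for example previous breastfeeding experience, education level and the mother's working situation. Include the BSES-SF only if it is measured at enrolment before any session; the Working Plan table gives no time for it. Infant age at enrolment is not a listed variable but could be derived from birth and visit dates.
- Fit this model whatever the observed balance, and report the unadjusted result alongside as secondary.
- Make the Abstract and items 2 and 3 say the same thing.

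The cost is wording, with no added data beyond fixing when the BSES-SF is taken if it is used. The downside is that the list must be agreed in advance and kept short, because ten centres support few covariates.
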